The Medical Research Council Unit The Gambia at London School of Hygiene & Tropical Medicine (MRCG at LSHTM) has a long history investigating the burden of pneumococcal disease and pneumococcal vaccination. In 2000–2004, a trial of a 9-valent PCV (PCV9) was conducted in Central and Upper River Regions (CRR and URR) of The Gambia. Vaccine efficacy in children aged 3–29 months was 37% against radiological pneumonia, 77% against vaccine-type (VT) invasive pneumococcal disease (IPD), and 16% against all-cause mortality [8]. In 2009, The Gambia introduced PCV7 into the routine EPI using a three-dose schedule without a booster dose (i.e. a ‘3 + 0’ schedule). In 2011, PCV7 was replaced by PCV13. The Pneumococcal Surveillance Project (PSP) has documented the impact of PCV13 in the Basse Health & Demographic Surveillance System (BHDSS) in rural Gambia. Four to five years after the introduction of PCV7/13 the incidence of VT IPD had declined by 82%, with a 24% reduction in radiological pneumonia, and 61% reduction in severe hypoxic pneumonia in children aged 2–59 months [9, 10]. Eight years after the introduction of PCV7/13 the incidence of VT IPD in the 2–59 month age group has declined by 92% and radiological pneumonia has declined by 33% [11]. Before the introduction of PCV, PSP detected an average of 35 annual cases of VT IPD among children aged 2–59 months. In 2016, we detected six cases of VT IPD, and in 2017, we detected three. In 2016/2017, we detected zero cases of VT IPD among children in the first year of life. These data indicate that the introduction of PCV7/13 has now controlled VT IPD.

It is now evident that following the introduction of PCV13, herd protection has developed in The Gambia. The annual count of VT IPD in older children in PSP was six to ten before the introduction of PCV13 in 2011. Following the introduction of PCV13 the annual case counts in 2015, 2016, and 2017 were four, one, and zero, respectively. In the 5–14 year age group, IPD incidence declined by 69% (95%CI, − 28–91%) and radiological pneumonia by 27% (95%CI, − 5–49%) [11]. Similar findings of the direct and herd effect of PCV are evident in Kenya [12, 13].

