### Outcomes {12}

The outcomes in the trial and the timing of their measurement are shown in Fig. 3. The primary trial endpoint is:
NP carriage of VT pneumococci in children aged 2 weeks–59 months with clinical pneumonia presenting to health facilities in the study area (measured in year 4).

Secondary endpoints will be:
NP carriage of non-vaccine type (NVT) pneumococci in children aged 2 weeks–59 months with clinical pneumonia presenting to health facilities in the study area (measured in year 4).Population-based and age-stratified NP carriage prevalence of VT and NVT pneumococci (measured in years 2 and 4).NP carriage of VT and NVT pneumococci in infants presenting for the first dose of PCV aged 6–12 weeks (measured in year 4).Incidence of radiological pneumonia in children aged 2 weeks–59 months (safety endpoint).Incidence of clinical pneumonia in children aged 2 weeks–59 months (safety endpoint).Incidence of clinical pneumonia associated with NP carriage of VT and NVT pneumococci in children aged 2 weeks–59 months (safety endpoint).Incidence of serotype-specific IPD in children aged 2 weeks–59 months (safety endpoint).Incidence of hospitalisation in children aged 2 weeks–59 months (safety endpoint).Mortality rate in children aged 2 weeks–59 months (safety endpoint).

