In order to isolate the herd effects of the schedules in very young infants, the secondary endpoint of VT carriage prevalence in infants aged 6–12 weeks presenting for their first dose of PCV13 will be measured in a cross-sectional manner in year 4 (Fig. 3). Safety endpoints covering the incidence of clinical pneumonia, radiological pneumonia, IPD, hospitalisation and mortality will be measured throughout the 4 years of the trial (Fig. 3). The incidence of clinical pneumonia associated with NP carriage of VT and NVT pneumococci will also be measured.

The dynamics of age-dependent VT pneumococcal transmission are complex and vary by population, contact patterns and the related carriage data have important implications on accurate vaccine protection estimates [39, 40]. Including an interpersonal contact pattern survey in Year 2 parallel with the survey of VT carriage will generate data on contact patterns for planned mathematical modelling of the effect of alternative PCV schedules. The parallel surveys will give insight into the magnitude of association between age-related carriage prevalence and rates of interpersonal contact and whether infection is associated with physical or non-physical contacts.

The emergence of NVT serotypes causing IPD in both children and adults following the introduction of PCV13 has been a source of concern. The effect of an alternative schedule on serotype replacement dynamics has not been well described. The measurement of NVT pneumococcal carriage in the population in years 2 and 4 will provide data on the effect of the alternative schedule on NVT pneumococcal transmission

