## Assignment of interventions: blinding

### Who will be blinded {17a}

Vaccinators and parents may be aware of the schedules used. Laboratory staff are blinded as specimens are labelled with a unique identification number that does not identify the study group. Blinding of laboratory staff will avoid bias given the laboratory-based measurement of the primary endpoint. Statisticians will analyse data in a pseudo-blinded fashion with the two groups identified by an indicator label rather than the identity of each group.

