We have *a priori* interest to examine the following potential effect modifiers: (a) age (2–12 weeks, 13 weeks–9 months, 10–23 months and 24–59 months), (b) inpatient/outpatient status and c) severity (severe pneumonia defined as clinical pneumonia with O_2_ saturation < 92%). The number of cases of each endpoint in the subgroups above may not be sufficient to assess non-inferiority in those strata but may enable the detection of differences in effectiveness between groups. We will examine the strength of evidence for differences between subgroups using interaction tests.

A secondary exploratory measurement and analysis of the primary endpoint will be conducted in year 2 of the trial, in order to detect potential early development of superior impact in the 1 + 1 group. This secondary hypothesis is different to the primary hypothesis of non-inferiority and will use an alpha value of 0.05, as will the final analysis.

The secondary endpoints of community pneumococcal carriage will be measured in years 2 and 4 of the study while carriage in infants aged 6–12 weeks presenting for their first dose of PCV will be measured in year 4. Comparison of the two groups will be presented as a prevalence ratio (and 95% confidence intervals). The same analytical methods as the primary endpoint analysis will be used to account for cluster-level non-independence and the allocation of clusters. We will use the same non-inferiority measurement as the primary endpoint, where non-inferiority will be established if the upper-limit of the confidence interval around the prevalence ratio for VT carriage in the 1 + 1 versus 3 + 0 clusters is ≤1.38.

An exploratory analysis will be performed to measure the association between age-specific contact pattern frequencies and pneumococcal carriage. The association between physical and non-physical contact frequency and age-specific pneumococcal carriage will be analysed using GEE models.

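### Inpatient status and severity are tested as effect modifiers of the vaccine-type carriage ratio, although both arise after randomisation and the schedule may change them

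*Protocol article*

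**What the plan says.** Statistical methods for primary and secondary outcomes {20a} states an a priori interest in three potential effect modifiers: age in four bands, "b) inpatient/outpatient status and c) severity". Severe pneumonia is defined there as clinical pneumonia with oxygen saturation below 92%. On the analysis it says: "We will examine the strength of evidence for differences between subgroups using interaction tests". It warns that numbers may be too small to assess non-inferiority within strata, and continues: "but may enable the detection of differences in effectiveness between groups". Small numbers are the only caution given.

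Outcomes {12} lists among the endpoints compared between arms: "Incidence of hospitalisation in children aged 2 weeks–59 months (safety endpoint". Justification of outcomes adds: "The incidence of clinical pneumonia associated with NP carriage of VT and NVT pneumococci will also be measured". Under Sample size {14}, the primary outcome is measured in random samples of participants within each of the 68 clusters.

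**The concern.** An interaction test supports a statement about effect modification when the subgroup variable is not itself changed by the intervention. Age meets that condition. Admission and hypoxia do not clearly meet it. Both belong to the episode at which the swab is taken, and VT disease can cause both. The protocol treats hospitalisation as an outcome. Background and rationale {6a} also reports a "61% reduction in severe hypoxic pneumonia in children aged 2–59 months" after vaccine introduction, against 24% for radiological pneumonia, so the severity mix moved over that period. Admission may also depend on judgement in an open trial: "Vaccinators and parents may be aware of the schedules used".

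If a schedule changes how often VT-positive cases become severe, it moves VT-positive children from one stratum to the other. VT prevalence then rises in one stratum and falls in the other. More severe VT disease under 1+1 would look like a carriage benefit in the larger, non-severe group, and milder disease would look like a carriage harm there. A significant interaction could then be read as differing effectiveness, in the subgroups that a reader concerned with safety is likely to consult.

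**Working it through.** The protocol gives no proportion severe or admitted and no subgroup power, so there is no stated figure to reproduce for this point. Inputs taken from Sample size {14} are 13% VT carriage in both arms, 1980 children per arm, and the design effect, which reproduces as 1 + (60 − 1) × 0.02 = 2.18. The severity proportions and multipliers below are assumptions.

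**Illustration 1.** Per case in either arm, VT carriage is 0.13. In 3+0, 10% of cases are severe regardless of carriage, so VT-severe = 0.13 × 0.10 = 0.013 and other severe = 0.87 × 0.10 = 0.087. VT prevalence is then 13% in both 3+0 strata. In 1+1, only the risk of severe illness among VT carriers is changed.

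- Doubled, severe: 0.026 / (0.087 + 0.026) = 0.026 / 0.113 = 0.230; ratio 0.230 / 0.13 = 1.77.
- Doubled, non-severe: (0.13 − 0.026) / (1 − 0.113) = 0.104 / 0.887 = 0.117; ratio 0.90.
- Halved, severe: 0.0065 / 0.0935 = 0.070; ratio 0.53.
- Halved, non-severe: 0.1235 / 0.9065 = 0.136; ratio 1.05.
- Overall, in both cases: 0.13 / 0.13 = 1.00.

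**Illustration 2, with milder multipliers.** In 3+0, 20% of non-carriers and 30% of VT carriers are severe or admitted. The severe stratum has VT prevalence 0.039 / 0.213 = 0.183 and the non-severe stratum 0.091 / 0.787 = 0.116. The true carriage ratio is 1.00.

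| Carrier risk multiplied in 1+1 by | Severe ratio | Non-severe ratio |
|---|---|---|
| 0.6 | 0.65 | 1.15 |
| 0.8 | 0.83 | 1.08 |
| 1.0 | 1.00 | 1.00 |
| 1.25 | 1.20 | 0.90 |
| 1.5 | 1.37 | 0.81 |

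For the first row, 0.0234 / 0.1974 = 0.119 against 0.183, and 0.1066 / 0.8026 = 0.133 against 0.116. If non-carrier severity ranges from 10% to 30%, with carriers 1.5 times as likely to be severe, the 0.6 multiplier gives 0.65 in the severe stratum and 1.06 to 1.28 in the other.

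**Chance of a significant interaction in the 0.6 row.** The difference in log ratios is ln(0.647) − ln(1.149) = −0.573. With 1980 per arm, the variance of the difference, summing (1 − p)/(np) over the four cells, is 0.0106 + 0.0190 + 0.0049 + 0.0041 = 0.0386, so the standard error is 0.197 and z = 2.92. At two-sided 0.05 the test is significant in about 83% of trials. With the full design effect the standard error is 0.197 × √2.18 = 0.290, z = 1.98, and the figure is about 51%. No child has a different carriage effect in this scenario.

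**When the reversal does not occur.** If the schedule acts only through carriage, with carriers 0.5 to 3 times as likely to be severe as non-carriers in both arms, a true ratio of 1.20 gives 1.15 to 1.22 across both strata. If the schedule multiplies severity equally in carriers and non-carriers (by 0.7 or 1.3, otherwise as in illustration 2), the severe ratio stays at 1.00 and the non-severe ratio is 1.04 or 0.95.

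**The case against.** The primary endpoint itself conditions on clinical pneumonia, which is also a post-randomisation event that vaccination can change. Inpatient and hypoxic pneumonia are narrower case definitions of the same kind, and Justification of outcomes defends measuring carriage among cases. This stands: a related selection applies to the primary contrast, and the difference is partly one of degree. What the subgroup tests add is a claim that effectiveness differs between kinds of children, and these strata cannot support that claim by themselves.

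The text speaks of effectiveness, not specifically of effectiveness on carriage, and a severe-stratum ratio of 1.77 would point a safety reader in the right direction. That also stands, but the companion ratio of 0.90 points the other way, and the interaction test cannot separate altered progression from a differing carriage effect.

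The severity proportions and multipliers are assumed. A reader might infer from the 61% fall in hypoxic pneumonia that the two schedules differ in severity given carriage. The documents do not support that. The figure compares periods before and after vaccine introduction, when VT carriage also fell steeply, and says nothing direct about two active PCV13 schedules.

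Separate incidence endpoints for hospitalisation, radiological pneumonia, IPD, mortality and carriage-associated pneumonia are already planned, as are community carriage surveys. Safety therefore does not depend on these interaction tests. The analysis plan, which is not shown, might add a caution on interpretation. The protocol nevertheless already names these two variables as effect modifiers and specifies the test.

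**Conclusion.** The point holds in a limited form. Inpatient status and severity are unsuitable for an effect-modification test of the VT-carriage prevalence ratio, because both belong to the post-randomisation episode and the schedule may change them. Where the schedules alter progression to severe illness or admission among VT carriers, and not among non-carriers, the stratum ratios can fall on opposite sides of 1 with an unchanged carriage effect: 1.77 and 0.90, or 0.53 and 1.05, in the first illustration, and smaller shifts under milder assumptions. Where the schedule acts only through carriage, the direction is kept. The documents do not establish which case applies.

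A reader might go further and infer that the non-inferiority conclusion is compromised. It is not: that decision rests on the overall prevalence ratio against 1.38, and no decision rule uses these subgroups. The consequence is confined to the interpretation of two secondary subgroup analyses, and the change is a worthwhile, inexpensive improvement.

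**What to change.** - Keep the effect-modification interaction test for age.
- Present VT prevalences and ratios by inpatient status and by severity as descriptive, and label the strata as post-randomisation ones that the schedule may affect. Do not read them as effect modification.
- Split the already planned incidence of VT- and NVT-associated clinical pneumonia by admission and by severity. Report arm rate ratios per child-year over the surveillance denominators, with the cluster-level allowance used elsewhere. This compares the randomised arms over the whole resident child population without conditioning on the episode's course.
- Where only a random sample of swabs per cluster is tested, weight by the inverse of the sampling fraction.

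The change needs revised analysis wording and uses swabs already planned for collection. The cost is that there is no interaction p-value for these two variables, and the split incidence rates need some extra weighting and lose some precision.

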### Interim analyses {21b}

There are no planned formal interim analyses.

### Methods for additional analyses (e.g. subgroup analyses) {20b}

An exploratory analysis to estimate the magnitude of the herd impact comparing endpoints in unvaccinated children across the two trial groups. This analysis may be limited by the low proportion of children that are unvaccinated.

### Analysis methods to handle non-adherence or missing data {20c}

The clusters will be analysed according to their random allocation. A per-protocol analysis will be performed including clusters that achieve pre-set thresholds for coverage of completed vaccine schedules. An intention to treat analysis will also be performed including all clusters. Sensitivity analyses will include a cluster-level term for the proportion of participants complying with the allocated schedule.

### Plans to give access to the full protocol, participant level-data and statistical code {31c}

The protocol is available on request. The data generated will be suitable for sharing in an anonymised format. The data will be in CDISC ODM format that is an internationally recognised standard. Data will not be deposited into a central repository but held securely by MRCG. The trial is registered with the International Society Clinical Trial Registry Network (ISCTRN) to maximise its visibility to other interested parties. Summary data will be provided through ISCTRN at the end of the study. Data sharing will follow MRC policy [51]. Access to the complete datasets will need to be approved by application to the MRCG Unit’s Archives department who will then forward it to the Scientific Coordinating Committee (SCC) of the Unit. All requests for the dataset will be reviewed by the SCC and also by The Gambia Government/MRC Joint Ethics Committee (GG/MRCG JEC) to establish that the request is in order to perform scientifically appropriate analysis. The datasets collected within the trial will be available to other users once all relevant trial-related publications in scientific journals have been accepted. Prior to this point, requests will be considered on a case by case basis.
For practical reasons this time period may be indicative and might need to be revised if delays occur. Different periods may be applied to different datasets, e.g. to take into account the complexity of cleaning and documentation.Timing will depend on the trial’s collection patterns.In relation to timing, the terms could, for instance, be expressed as follows: ‘6-months after the end of the current grant period’, ‘12-months after new data collection to allow for data cleaning and documentation’, or ‘3-months following the first publication of findings based on the data’.

Statistical code will be available on request.

## Oversight and monitoring

### Composition of the coordinating centre and trial steering committee {5d}

The trial management group meets every week and includes the Principle Investigator, Trial Epidemiologist, Trial Coordinator, Data Manager, and Higher Laboratory Scientific Officer. The Trial Steering Committee (TSC) is composed of a Chairperson, an expert clinician, an expert trialist, an expert laboratory scientist, the national EPI Programme Manager, a member of the URR RHD, two community representatives, and a Sponsor representative. The TSC meets one to two months after every DMC meeting. The TSC sets targets for recruitment, data collection, and protocol compliance. All trial-related complaints are reviewed by the TSC. A statistical analysis plan will be approved by the TSC. The TSC considers new information relevant to the trial, including reports from the DMC and the results of other studies that may have a direct bearing on the future conduct of the trial.

### Composition of the data monitoring committee, its role and reporting structure {21a}

The DMC is independent of the Sponsor and composed of a Chairperson, expert clinician, expert statistician, and an independent statistician. The role of the DMC is described in its Charter (see Supplementary material) and is to protect and serve trial participants and to assist and advise the PI so as to protect the validity and credibility of the trial. The DMC monitors the safety of the trial, reviews its progress and accruing data, makes recommendations to the TSC whether the trial should continue, be terminated, or modified, and determines if interim analyses should be undertaken. The DMC also considers data quality, recruitment, compliance with the protocol, sample size assumptions, data emerging from other related studies, requests for interim trial data, and the final data and its interpretation. Materials and discussion during meetings are confidential. The DMC meets every 4–6 months.

### Adverse event reporting and harms {22}

Adverse events are defined according to the ICH Harmonised Guideline for GCP E6(R2). Due to the established safety record of PCV13 the trial does not record solicited events of reactogenicity. The trial uses an electronic vaccine record system to record unsolicited events of reactogenicity when reported by caregivers within 7 days of a dose of PCV. Serious adverse events (SAEs) are tabulated in reports every 3 months. Severe adverse drug reactions (SADR) and serious, severe unexpected serious adverse reactions (SUSAR) are reported to the Sponsor within 24 h. The Sponsor reports SADRs and SUSARS to the Gambia Medicines Control Agency (GMCA), while PI reports these events to the Gambia Government/MRCG Joint Ethics Committee (GG/MRCG JEC), LSHTM Ethics Committee (LSHTM EC), TSC, and DMC.

Follow-up and resolution of SAEs is recorded in electronic reports. The Sponsor, TSC and DMC are informed of SAEs at each meeting. The MRCG Clinical Trials Department Coordinator reports SAEs to the national Regulatory Authority (RA) Gambia Medicine Control Agency (GMCA). The PI reports SAEs to the TSC, DMC, and MoH. SADRs and SUSARs are reported to the GG/MRC JEC within 5 working days. Deaths unrelated to the intervention are reported to the GG/MRC JEC at the next meeting. Information on unanticipated changes that may increase the risk to participants or may affect adversely the safety of the participants or the conduct of the trial or that could alter the EC’s approval to continue the trial will be reported to the Sponsor, GG/MRC JEC, LSHTM EC, GMCA, TSC, and DMC in writing within 2 working days.

### Frequency and plans for auditing trial conduct {23}

The GG/MRCG JEC may audit the conduct of the trial at any time, independent of the investigators and Sponsor. The trial management group meets weekly to review progress in recruitment, clinical endpoint surveillance, and data quality. The trial management group meets monthly to review standardised indicators of quality assurance of all study procedures and complaints. The TSC meets one to two months after every DMC meeting, which occurs approximately every 4–6 months. The TSC sets targets for recruitment, data collection, and protocol compliance. All trial-related complaints are reviewed by the TSC. The trial statistical analysis plan will be submitted for approval by the TSC. The TSC considers new information relevant to the trial, including reports from the DMC and the results of other studies that may have a direct bearing on the future conduct of the trial. Annual reports are submitted to the GG/MRCG JEC and LSHTM EC which document progress in recruitment, SAEs, and protocol deviations and violations.

